### Randomization and masking

2.5

Patients will be assigned a study (patient) number after consenting to the study. Patients who meet all criteria for enrollment will be randomized to double-blind treatment in a 2:1 ratio. Assignment to treatment groups will be determined by a computer-generated random sequence. SQJZ and placebo is numbered in advance and will be dispensed in sequence. The placebo is made of SQJZ (5%) and dextrin (95%) to insure the mimic appearance, smell, and taste.^[29]^ Both researchers and participants will not know the assignment. The information on intervention assignments will be stored in the third consulting center of biomedical statistics.

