### Outcome measures and safety

2.6

The primary outcome will be NMSS, a validated tool for rating frequency and severity of NMS in PD.^[30]^ NMSS domains are as follows: cardiovascular, including falls; sleep/fatigue; mood/cognition; perceptual problems/hallucinations; attention/memory; gastrointestinal tract; urinary; sexual function; miscellaneous. NMSS use a 4-point scale to describe severity and frequency, and higher score indicates more severe conditions. The total NMSS score ranges from 0 to 350. Secondary endpoints include Unified Parkinson Disease Rating Scale (UPDRS),^[31]^ Parkinson Disease Questionnaire-39 (PDQ-39),^[32]^ Parkinson Disease Sleep Scale (PDSS),^[33]^ Parkinson Fatigue Scale (PFS-16),^[34]^ and the constipation severity instrument (CSI).^[35]^ The NMSS, UPDRS, PDSS, PFS-16, and CSI will be assessed at baseline, 4 weeks, 8 weeks, 12 weeks, and 24 weeks. Considering that the quality of life will not be changed in a matter of weeks, the PDQ-39 will be documented at baseline, 12 weeks, and 24 weeks.

During the course of the trial, safety will be assessed through laboratory testing and ECG. Laboratory testing will include liver function and renal function which herbal medicines may injure in the past reports. Participants will get safety assessment at baseline, 4 weeks, and 12 weeks. Investigators are responsible for monitoring the safety of patients who have entered this study. The occurrence and nature of pre-existing conditions including clinically significant signs and symptoms of the disease under treatment in the study will be recorded. Any unfavorable and unintended sign (including an abnormal laboratory finding), symptom, or disease after randomization will be reported as an adverse event, whether or not related to the investigational drug. Adverse events’ record will follow the WHO Adverse Reaction Terminology. Severe adverse events will be reported to Ethics Committee and principal investigator, and be assessed to determine whether further diagnostic investigation or treatment is warranted. If a severe adverse event occurs, appropriate treatment and follow-up will be given.

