### Statistical analysis

2.8

The analysis of the primary variable will be based on the full analysis set: all randomized, treated patients who had a baseline and at least 1 postbaseline measurement for the primary variable. Only when the participant is not taking any drugs after randomization can he be ruled out. For missing value caused by dropout, the remaining date will use the last observation to carry forward. For missing value in the middle of complete cases, the most recent value of not missing date will be carried forward. Analyses of the safety data will be based on the safety set: all patients who were receiving at least 1 dose of trial medication.

Baseline demographic and clinical characteristics will be tabulated as means and standard deviations for continuous variables, and proportions and percentages for categorical variables. Standard baseline characteristics of sex, age, and medical history will be summarized for all patients. Group comparisons will be made using Fisher exact test for categorical data and analysis of variance, with independent factors for treatment of continuous data.

The primary objective of this study is to test the hypothesis that Chinese herbal formula SQJZ will benefit PD patients in alleviating NMS. Mixed-model repeated-measures analyses will be used to assess between-group differences in the modeled change in scores from baseline to 24 weeks. The change score from baseline at each visit will be the dependent variable. Independent variables in the model for fixed effects will be treatment (2 levels: SQJZ and placebo), visit (5 levels: baseline, week 4, week 8, week 12, and week 24), treatment-by-visit interaction, concomitant treatment (yes or no), baseline measures (UPDRS, NMSS), sex, age, and so on. An unstructured covariance matrix will be used to model the within-patient variance–covariance errors. If the unstructured covariance structure matrix results in a lack of convergence, the heterogeneous Toeplitz covariance structure followed by the heterogeneous autoregressive covariance structure will be used. The Kenward–Roger approximation will be used to estimate the denominator degrees of freedom. Similar methods will be used for assessment of secondary endpoints.

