### Sample size

2.9

According to a previous study,^[14]^ we assumed the effect size of 0.4 in SQJZ treatment compared to placebo at 12 weeks, then a minimum of 204 patients (136 for SQJZ and 68 for placebo). In consideration of a dropout of about 15%, about 240 patients will be needed to achieve a sufficient statistical power of 85% at a significance level (alpha) of 0.05 in 2-tailed test.

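### The primary mixed model gives baseline NMSS one slope for all visits; a baseline-by-visit term would be a minor, nearly free gain in precision, mainly at week 24

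*Protocol article*

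**What the plan says.** Section 2.8 (Statistical analysis) plans a mixed model for repeated measures to assess "between-group differences in the modeled change in scores from baseline to 24 weeks". The dependent variable is change from baseline at each visit. The fixed effects are treatment, visit, "treatment-by-visit interaction, concomitant treatment (yes or no), baseline measures (UPDRS, NMSS" scores), sex and age, and the list is then left open. Residuals have an unstructured covariance matrix, with two fallback structures and Kenward–Roger degrees of freedom. The same section fills values missing after dropout by LOCF, and says that secondary endpoints will be handled in a similar way.

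Section 2.6 (Outcome measures and safety) states that NMSS, UPDRS, PDSS, PFS-16 and CSI "will be assessed at baseline, 4 weeks, 8 weeks, 12 weeks, and 24 weeks". PDQ-39 is measured at baseline, week 12 and week 24 only. Treatment lasts 12 weeks, so the week-24 visit comes 12 weeks after it ends.

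Section 2.9 (Sample size) rests on week 12: "we assumed the effect size of 0.4 in SQJZ treatment compared to placebo at 12 weeks".

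**The concern.** When change from baseline is regressed on baseline and the SDs are equal, the slope at a visit is the correlation of that visit with baseline, minus 1. A single slope therefore requires that correlation to be the same at weeks 4, 8, 12 and 24. Correlations usually weaken as visits move apart, and here the last gap is 12 weeks, all of it off treatment. If they do weaken, the shared slope is drawn towards the early, less variable visits and is too shallow for the later ones.

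What is at stake is precision. At a visit where the slope is wrong, chance imbalance in baseline NMSS is not fully removed and the residual variance is larger than it need be. The model is said to run to week 24, where the misfit would be greatest.

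**Working it through.** **Inputs from the documents.** Allocation is "randomized to double-blind treatment in a 2:1 ratio", about 240 patients (160 and 80) are randomised, and there are four post-baseline visits at weeks 4, 8, 12 and 24. The documents give no SD, correlation or slope for NMSS by visit, so the correlation patterns below are assumptions. Only post-baseline rows are modelled. Section 2.8 also lists baseline as a level of visit, although change there is always zero; that is a separate matter.

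**The plan's own figure.** The plan gives no number for the slope. Its only related figures are "a minimum of 204 patients (136 for SQJZ and 68 for placebo") and "sufficient statistical power of 85% at a significance level (alpha) of 0.05 in 2-tailed test". With effect 0.4 and 2:1 allocation, the placebo group needs (1.960 + 1.036)² × 1.5 / 0.16 = 84.2, so 85, and 255 in total. The stated 204 is what one-sided alpha gives: (1.645 + 1.036)² × 1.5 / 0.16 = 67.4, so 68 and 136. Two-sided power is 76.8% with 204 patients and 83.2% with 240. This matters here only as the reference for power.

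**Formula for precision.** Take unit SDs, visit-specific slopes β_j and residual covariance S. The shared slope b solves b = 1′S*⁻¹β / 1′S*⁻¹1, where S* = S + (β − b)(β − b)′. The variance of the contrast at visit j is then multiplied by 1 + (β_j − b)² / S_jj.

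**Worked example: correlation 0.85 per 4 weeks.** The slopes are −0.150, −0.278, −0.386 and −0.623 (the last from 0.85⁶ − 1). The shared slope is b = −0.235.
- Week 12: 1 + (0.1507)² / 0.623 = 1.036.
- Week 24: 1 + (0.388)² / 0.858 = 1.175.

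| Assumed pattern | Week 12 variance | Week 24 variance |
|---|---|---|
| 0.85 per 4 weeks | +3.6% | +17.5% |
| 0.90 per 4 weeks | +3.5% | +14.8% |
| Random intercept 0.5 plus 0.7 per 4 weeks | +2.0% | +6.9% |
| The same three with 15% measurement error | +0.5 to 0.8% | +3.0 to 8.5% |

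In the first row this equals setting aside 240 × (1 − 1/1.036), about 8 patients, at week 12 and 240 × (1 − 1/1.175), about 36, at week 24. If the SDs are also allowed to differ between visits, the week-12 figure can reach 8%.

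**Check by simulation.** A mixed model with unstructured covariance was fitted to 300,000 simulated patients, with SEs rescaled to 240. Correlations of baseline with the four visits were mild (.80/.77/.74/.68), moderate (.80/.74/.68/.52) or strong (.85/.75/.65/.40) in their decline. The figures are SEs with the shared slope over SEs with visit-specific slopes, complete data.

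| Decline | Week 12 | Week 24 |
|---|---|---|
| Mild | 0.0919 / 0.0919 (+0%) | 0.1008 / 0.1003 (+0.5%) |
| Moderate | 0.1004 / 0.1003 (+0.1%) | 0.1197 / 0.1168 (+2.5%) |
| Strong | 0.1052 / 0.1041 (+1.1%) | 0.1350 / 0.1257 (+7.4%) |

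Squared, the week-24 ratios are about +1%, +5% and +15% of variance, in line with the formula. With random 15% dropout filled by LOCF, the week-24 SE loss is 0.3%, 2.0% and 6.3%.

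**Power at week 12.** With 240 patients and effect 0.4, an SE larger by 1.1% moves power from 83.2% to 82.4%, and 3.6% more variance moves it to 81.9%.

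**Bias.** Dropout of about 15% was related to baseline in opposite directions in the two arms. The figures are bias in SD at week 24, for mild, moderate and strong decline; simulation error is about 0.004 SD.

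| Data analysed | Shared slope | Visit-specific slopes |
|---|---|---|
| Observed only | −0.013, −0.060, −0.103 | 0.005, −0.004, −0.001 |
| LOCF, as planned | −0.005, −0.046, −0.077 | −0.005, −0.046, −0.078 |

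At week 12 under LOCF the bias is −0.026, −0.035 and −0.047 with either model. When dropout depends on baseline alike in both arms, the two models differ by at most 0.003 SD.

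**The case against.** One slope shared by all visits is a legitimate model. Without dropout, randomisation keeps the treatment contrast unbiased whatever slope is used. The decline in correlation appears nowhere in the documents, and the loss runs down to nothing when it is absent. At week 12, the only time point that the sample size names, the loss is slight. The covariate list is open-ended, the article is condensed, and an analysis plan that is not shown may add the term.

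Most of this stands and limits the point to a minor one. The last part carries less weight. Section 2.8 goes as far as naming covariance fallbacks and the degrees-of-freedom method, and it names one interaction. The open ending follows sex and age, so it reads most naturally as further covariates rather than further interactions.

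A reader might infer more: that the shared slope biases the week-12 and week-24 contrasts when dropout depends on baseline. The documents do not support that. The model is to be fitted to data completed by LOCF, and there the bias is the same with and without the extra term. Removing it by visit-specific slopes would require analysing observed data only, together with dropout related to baseline differently in the two arms, which nothing in the documents suggests. A reader might also turn the week-24 loss into lost power by carrying the effect of 0.4 forward. Section 2.9 assumes that effect at week 12 only, and no week-24 effect is given.

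**Conclusion.** The point holds as a matter of precision. As listed, the primary model fixes one baseline NMSS slope across four visits. Provided that the correlation with baseline declines over time, and with equal SDs, the cost is roughly 0 to 4% of contrast variance at week 12 and about 1 to 18% at week 24. The top of the week-24 range needs a steep decline. The cost at week 12 is about one percentage point of power or less in the patterns worked above. With equal slopes there is no cost.

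It is not an error that biases the planned analysis. A benefit for bias would arise only if LOCF were dropped and the mixed model fitted to observed data, under baseline-related dropout that differs by arm. The point is minor and worth taking because the change is almost free.

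**What to change.** In section 2.8, add a baseline NMSS-by-visit interaction to the fixed effects of the primary model, with visit categorical and restricted to weeks 4, 8, 12 and 24. For each secondary endpoint, state that its own baseline value and that baseline's interaction with visit are included; for PDQ-39 the visits are weeks 12 and 24. Carry the same wording into the analysis plan, and fix it before unblinding.

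The cost is one line of text and three extra parameters in the primary model with about 240 patients. No new data are needed. If the slopes prove equal, the only loss is a negligible number of degrees of freedom. This change does not deal with any bias from LOCF, which is a separate decision.

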### Sample size

2.9

According to a previous study,^[14]^ we assumed the effect size of 0.4 in SQJZ treatment compared to placebo at 12 weeks, then a minimum of 204 patients (136 for SQJZ and 68 for placebo). In consideration of a dropout of about 15%, about 240 patients will be needed to achieve a sufficient statistical power of 85% at a significance level (alpha) of 0.05 in 2-tailed test.

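### The sample size of 204 evaluable (240 randomised) gives about 76% power in a two-tailed test at 0.05, not the stated 85%; it matches a one-tailed calculation

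*Protocol article*

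**What the plan says.** Section 2.9 of the protocol article gives every input to the calculation. For the effect it says "we assumed the effect size of 0.4 in SQJZ treatment compared to placebo at 12 weeks". From this it derives "a minimum of 204 patients (136 for SQJZ and 68 for placebo" in the placebo arm. It then allows for a dropout of about 15% and concludes that "about 240 patients will be needed to achieve a sufficient statistical power of 85% at a significance level (alpha) of 0.05 in 2-tailed test".

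Section 2.5 (Randomization and masking) confirms the 2:1 allocation. Section 2.8 (Statistical analysis) plans a mixed model for repeated measures on change scores. Its covariates include baseline NMSS, baseline UPDRS, sex and age, and it carries the last observation forward for dropouts. The article nowhere mentions a one-tailed test. Section 2.9 does not refer to covariate adjustment or to a gain from repeated measures.

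**The concern.** Effect size, allocation, alpha, sidedness and power together determine the sample size. The printed total is about a fifth smaller than the stated two-tailed inputs require, which is too much for rounding.

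Two things are at stake. First, the stated power is what a reader relies on when interpreting a null result. A trial described as having 85% power is read as having a 15% risk of missing the assumed effect; if the true figure is about 24%, a negative result says less than it appears to. Second, the mismatch leaves the intended test in doubt. If the final analysis followed the calculation rather than the label, a one-tailed test at 0.05 would double the false-positive rate in the favourable direction, from 0.025 to 0.05.

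**Working it through.** **Inputs.** All come from section 2.9, with the allocation also in section 2.5: effect size d = 0.4 (in SD units), SQJZ to placebo 2:1, alpha 0.05 two-tailed, power 85%, dropout 15%.

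**Formula.** For a comparison of two means with twice as many patients on SQJZ as on placebo,

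n(placebo) = (1 + 1/2) × (z_alpha + z_power)² / d², and n(SQJZ) = 2 × n(placebo).

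Here z_power = 1.036 for 85%. z_alpha is 1.960 for a two-tailed test at 0.05 and 1.645 for a one-tailed test.

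**Reproducing the printed figures.** They come out with the one-tailed value:

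- 1.5 × (1.645 + 1.036)² / 0.16 = 67.4, so 68 placebo and 136 SQJZ, 204 in total.
- 204 / 0.85 = 240 randomised.

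Both arms, the evaluable total and the inflated total agree exactly.

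**The test that the section names.** With the two-tailed value:

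- 1.5 × (1.960 + 1.036)² / 0.16 = 84.2, so 85 placebo and 170 SQJZ, 255 in total. The noncentral t distribution gives the same numbers.
- 255 / 0.85 = 300 randomised.
- The shortfall is 255 − 204 = 51 evaluable patients, 20% of the requirement.

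**Power of the printed sample size.** For 136 versus 68 the noncentrality is 0.4 / √(1/136 + 1/68) = 2.69. For 160 versus 80 (all 240 analysed) it is 0.4 / √(1/160 + 1/80) = 2.92.

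| Analysed (SQJZ/placebo) | Test at 0.05 | Power, normal approximation | Power, noncentral t |
|---|---|---|---|
| 136/68 | two-tailed | 76.8% | 76.4% |
| 136/68 | one-tailed | 85.3% | 85.1% |
| 160/80 | two-tailed | 83.2% | 82.9% |
| 170/85 | two-tailed | – | 85.1% |

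**Detectable effect.** For 85% power in a two-tailed t-test, the effect has to be 0.447 with 136/68, or 0.412 with 160/80.

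**Other ways to reach 204.** Two-tailed variants at d = 0.4 do not give it: 2:1 at 80% power needs 222, 2:1 at 75% needs 198, and 1:1 at 85% needs 226.

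**The case against.** The strongest objection is that 76.4% is the power of an unadjusted t-test on 204 patients, and section 2.8 plans something else. Its model adjusts for baseline NMSS and other covariates. If 0.4 is standardised on the unadjusted SD, which section 2.9 does not say, adjustment replaces d by d / √(1 − r²), where r is the correlation between the covariates and the outcome. The values of r below are illustrative, since the article gives none.

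| Assumed r | Two-tailed power, 136/68 | Two-tailed power, 160/80 |
|---|---|---|
| 0 | 76% | 83% |
| 0.3 | 80% | 86% |
| 0.4 | 83% | 89% |
| 0.5 | 87% | 92% |

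Reaching 85% with 136/68 needs r of about 0.45, that is, about 20% of the variance explained. In addition, the full analysis set keeps treated patients who have a baseline and one later measurement, and carries their last value forward. The number analysed may therefore be nearer 240 than 204.

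This stands as a limit on what can be said about the power of the final analysis. It does not rescue the printed statement. Section 2.9 claims no adjustment, states no correlation, and itself sizes the trial on 204 patients after dropout. If 0.4 already refers to an adjusted SD, there is no gain at all. Values carried forward from early dropouts may also dilute a 12-week effect.

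A smaller point also stands: the one-tailed origin is inferred. The exact match makes it by far the likeliest explanation, but the article alone cannot show whether the sample size or the two-tailed label is the slip. Either way, the two do not agree.

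**Conclusion.** The statement in section 2.9 is wrong as written. For an unadjusted two-tailed comparison at 0.05 and an effect of 0.4, 136 versus 68 patients gives about 76% power, some 9 points below the stated 85%. The type II error is about 24% instead of 15%. With no loss at all, 240 patients give 82.9%.

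This takes the effect size of 0.4 as given; the study cited for it was not available, and the finding does not depend on it. It also assumes equal SDs in the two arms and no variance reduction from covariates, because the section states none. The error has to be corrected: power and sidedness are core reported design figures, and the contradiction follows from the section's own inputs.

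**What to change.** Correct the power statement in section 2.9, keep 240 randomised patients, and say explicitly that the primary test is two-sided. Suggested wording: *About 240 patients will be randomised 2:1. Allowing for 15% dropout, 204 evaluable patients (136 SQJZ, 68 placebo) give about 76% power to detect an effect size of 0.4 with a two-sided t-test at alpha 0.05, and 85% power for an effect size of about 0.45.*

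The sponsor may add the power of the baseline-adjusted model, provided that the assumed correlation between baseline and week 12 is given and the SD behind the 0.4 is defined. The shortfall should not be resolved by relabelling the test as one-tailed.

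This costs one sentence and a less favourable power figure, with no extra patients. If the sponsor prefers to keep 85% power at 0.4 without relying on adjustment, the alternative is about 255 evaluable and 300 randomised patients, 60 more than planned.

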### Protocol amendments and dissemination

2.10

If there is any amendment to the protocol, approval must again be sought from the ethics committee before implementation. Participants who are randomized to placebo group will get a 12-week SQJZ and follow-up as post-trial compensation. Participants’ personal information will be confidentiality. Only relevant code will be sent to statistic analysis. The final dataset will be available to the principal investigator and the independent statistician. Data will be stored in a locked cabinet at the Dongzhimen Hospital Beijing University of Chinese Medicine, China, for 5 years.

Results will be published on the website of ClinicalTrials.gov in accordance with the CONSORT2010 Statement. We envisage the results will be published in high-impact generalist and specialist journals.

## Discussion

3

Nonmotor symptoms are common in patients with established PD.^[1–4]^ The NMS of different race seems to be different. Recent memory (71.8%), constipation (68.2%), and attention dysfunction (62.4%) are the major NMS in Chinese PD patients, which shows great differences from western patients.^[36]^ Another study showed that NMS domains that influenced the PDQ-39 were sleep/fatigue, mood, gastrointestinal, urinary, and miscellaneous symptoms.^[37]^ These results strongly suggested that fatigue, sleep problems, and gastrointestinal symptoms play a key role in the life quality of PD patients. If there is a therapy directly aiming at these domains, it would be more helpful for Chinese PD patients.

The SQJZ formula is composited based on TCM practical experiences and TCM Ancient Books with the functions of Bushenjiannao (in Chinese, reinforcing kidney for better brain function), Ziyintongfu (in Chinese, nourishing Yin to treat constipation), and Qingreanshen (in Chinese, clearing interior heat to treat insomnia). It is believed to be suitable for dealing with complicated and diversified NMS, such as constipation, sleep disorder, and dizziness.^[22,38]^ There have been many clinical reports of Chinese herbal formula for treating NMS in PD patients, but disadvantages of trial design cannot underpin the long-term efficacy of TCM therapy. A good-quality controlled randomized clinical trial will bring credible evidence of efficacy and safety of SQJZ formula for treatment of NMS in PD patients.

This will be a study with restrictive inclusion, exclusion criteria, special instrument of NMS, and a clearly defined quality controlled intervention, and will be the first randomized controlled trial to evaluate the efficacy and safety of SQJZ formula in NMS of PD patients. Successful completion of this clinical trial may provide a new strategy in the treatment of PDNMS.
